### Randomization and blinding

GPs, who agree to participate, will be sequentially allocated to either the intervention or the control group by a trained staff member at the Institute of Social Medicine, Occupational Health and Public Health (ISAP) external to the project. Randomization will be done by adaptive randomization [28] applying the biased coin method and using a computerized random number generator. Given that the intervention is addressed at the practitioners, it is not possible to blind GPs to their group allocation. However, GPs will be blinded to knowledge of the primary outcome measures. Patients will be blinded with regard to the group allocation. Participating GPs will be informed about allocation to control or intervention group after randomization completion by postal mail including a sealed envelope with the assigned intervention category. They will further be sent recruitment material and consent forms for patients by postal mail. In addition, GPs will receive explanatory instructions about the recruitment material and the recruitment process by telephone through a research assistant who will not be involved with tracking of patient enrollment or data collection. GPs will receive an instruction how to recruit patients in a blinded manner. Practitioners will identify and recruit patients according to the inclusion and exclusion criteria within their practices. They will inform eligible patients about the study and ask them to participate. Information material and consent forms for patients are identical for intervention and control group. The statistician analyzing the data will be unaware of the group allocation. The investigator and the research team will remain blinded to the results until data collection is completed.

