### Intervention scheme

For the present study, we have developed a 30 min online-tutorial based on the 5As framework of obesity management by the CON which covers recommendations on how to discuss weight with the patient (ASK), assess obesity related risks and causes of weight gain (ASSESS), advise on treatment options (ADVISE), agree on weight loss expectations and treatment plan (AGREE) and assist the patient in the ongoing process of losing weight (ASISST). The 5As framework has the potential to improve weight management counselling to patients by encouraging GPs to start sensitive conversations with the patient and achieve agreement on weight management goals and strategies. A key principle of the 5As framework is to measure the success of weight management in improvements in overall health and well-being rather than in the amount of weight loss. The 5As online-tutorial includes five knowledge sections that cover the 5As and the current state of knowledge on obesity management. The online-tutorial contains a short knowledge quiz at the end. An overview of the 5As is provided in Fig. 1. The 5As online-tutorial will be implemented in cooperating primary health care practices. Participating GP practices will be randomly allocated either to the intervention group with continuous access to the 5As online tutorial or to the control group, where GPs will be assigned to a waiting list condition. Waiting list practices will gain access to the 5As online-tutorial 6 months after the trial ended. GPs of the intervention group will be sent access data to the 5As online-tutorial after return of the baseline questionnaire (BL) and will have continuous access to the 5As program throughout the trial. Intervention completion by GPs of the intervention group will be checked and GPs will be reminded to complete the 5As intervention within two months after gaining access to the tutorial. CME points (Continuing Medical Education) will be granted after completion of the intervention module. Patients with obesity will be recruited in cooperation with participating GP practices. Patients of both groups (intervention group, control group) will be assessed using comprehensive questionnaires at recruitment (baseline, BL) as well as 6 and 12 months follow-up (after recruitment). GPs of both groups will be asked to complete questionnaires at BL (after recruitment) and 12 months follow-up. Furthermore, GPs of both groups will be asked to assess the health and weight status of each of their recruited patients immediately after patient inclusion and 12 months after patient inclusion. Participating GPs and patients will be invited to complete the follow-up assessments by postal reminder. A flow diagram of the overall intervention scheme is provided in Fig. 2.

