### Inclusion/ exclusion criteria

No exclusion or inclusion criteria apply for the GPs. Patients will be recruited if they fall within the BMI and age range (BMI greater than 30 kg/m^2^, age 18 to 60 years) but do not present at the GPs with an acute illness that needs priority management. The criteria for inclusion and exclusion of participants are summarized in Table 1.

**Table 1 Tab1:** Criteria for inclusion and exclusion of participants

Criteria for inclusion:	
- Body mass index greater than 30 kg/m^2^	
- Age between 18 and 60 years	
- German as native language	
Criteria for exclusion:	
- Acute physical or mental illness that needs priority management and make study participation impossible according to the GP	

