### Data analysis

After completion of the trial data cleaning and quality control will be conducted. Prior to testing the effectiveness of the intervention, appropriate statistical tests will be used to examine possible baseline differences between groups (e.g. age, sex, educational level, employment status and marital status). Hierarchical regression models will be used to analyze treatment effects from baseline to follow up. Models will be adjusted for the baseline outcome value and confounding factors, such as age, sex and socio-economic background. All analyses will be intention-to-treat in order to control for non-random dropout effects. Patterns of missing values will be inspected and, if applicable, replaced using appropriate statistical methods. Additionally, the effect of the intervention on provider knowledge, satisfaction with own knowledge and perceived counseling behavior will be analyzed. The level of statistical significance will be set at *p* < 0.05 for all statistics.

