#### Power calculation and sample size

Based on previous research, a power based sample size calculation was done using Stata 13.1 SE software package (StataCorp LP, College Station, TX). The primary outcome measure, the 5A PACIC sum score, may yield a minimum of 15 points difference prior to post-intervention. With a power of 95% and a standard deviation of 20 points [27], a sample size of *n* = 47 participating patients for each group was estimated to detect group differences. Given a 30% drop-out-rate, which is based on previous work of the ISAP, the overall sample size would comprise *n* = 134. According to Rueda-Clausen et al. [27] 15 points were regarded as a clinical significant change in the 5A PACIC sum score. Taking into account the interclass correlation coefficient of 5% from the cluster randomization the sample size would increase slightly to *n* = 66 patients per group. Given the 30% drop-out-rate *n* = 86 patients were estimated for each group. We estimate that 6–7 patients per practice could be recruited into the trial. Therefore, the trial aims to enroll at least 20 GPs. The overall sample will comprise 172 patients and not less than 20 GPs.

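### The unit of randomisation is stated inconsistently (practice or individual GP), and nothing keeps GPs who share a practice in the same arm

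*Protocol article*

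**What the plan says.** Four sections of the protocol article bear on the unit.

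- **Intervention scheme** randomises practices: "Participating GP practices will be randomly allocated either to the intervention group with continuous access to the 5As online tutorial". The control condition is described at the same level: "Waiting list practices will gain access to the 5As online-tutorial 6 months after the trial ended".
- **Randomization and blinding**, the section that governs how allocation is done, randomises doctors one at a time: "GPs, who agree to participate, will be sequentially allocated to either the intervention or the control group". The method is a biased coin. Practice membership is not mentioned as something the procedure takes into account.
- **Inclusion/ exclusion criteria** places no limit on who may join from a practice: "No exclusion or inclusion criteria apply for the GPs".
- **Power calculation and sample size** moves between the two units in consecutive sentences: "We estimate that 6–7 patients per practice could be recruited into the trial", followed by "Therefore, the trial aims to enroll at least 20 GPs". The ICC of 5% is attributed to the cluster randomisation, without saying whether it applies to patients of one GP or of one practice.

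The analysis text is neutral on the matter: "Hierarchical regression models will be used to analyze treatment effects from baseline to follow up". It names no clustering level.

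**The concern.** In a cluster trial the randomised unit determines who can contaminate whom, how many clusters there are and which level the analysis must respect. Here the two descriptions are equivalent only if each practice contributes one GP, or if all GPs of a practice go to the same arm. The article states neither.

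Under the wording in Randomization and blinding, two doctors of one practice may both agree to take part and be allocated separately. One then completes the tutorial while the other is on the waiting list. The intervention is knowledge about counselling, which colleagues can share, and the primary outcome is the patient's account of counselling over the past six months. Any spill-over would therefore act directly on the primary endpoint and pull the arms together. Once a practice has been split, the analysis cannot readily recover the uncontaminated contrast.

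**Working it through.** **1. The sections side by side**

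| Section | Unit |
|---|---|
| Intervention scheme (allocation) | practice |
| Intervention scheme (waiting list) | practice |
| Randomization and blinding | individual GP, in sequence |
| Sample size, recruitment estimate | practice |
| Sample size, target | GP |
| Data analysis | not named |

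The step from patients per practice to a number of GPs works only if one GP stands for one practice. That is probably what was meant, but no rule makes it so.

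**2. The plan's own starting figure**

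Inputs from the sample size section: difference 15, SD 20, power 95%. Alpha is 0.05 from Data analysis; two-sided is assumed, because it reproduces the stated figure.

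n per arm = 2 × [20 × (1.960 + 1.645) / 15]² = 46.2, rounded up to 47. This agrees with the article.

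**3. One GP per practice**

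Design effect = 1 + (m − 1) × 0.05, where m is patients per cluster.

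- m = 6: 47 × 1.25 = 58.75, so 59 per arm
- m = 7: 47 × 1.30 = 61.1, so 62 per arm

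These results are the same whether the cluster is called a GP or a practice. (The article's 66 per group does not follow from 6–7 patients per cluster. That is a separate matter and does not depend on the label.)

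**4. Several GPs per practice, all kept in one arm**

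Assumptions, not in the documents: 6–7 patients per GP, and the ICC of 0.05 holds across the whole practice.

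| GPs per practice | m | Design effect | Needed per arm, analysed | Recruited per arm (÷ 0.7) |
|---|---|---|---|---|
| 2 | 12–14 | 1.55–1.65 | 73–78 | 105–112 |
| 3 | 18–21 | 1.85–2.00 | 87–94 | 125–135 |

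The plan recruits 86 per arm.

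**5. Power at the planned size**

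Analysed per arm: 86 × 0.7 = 60. Effective n = 60 / design effect. Power = Φ[(15/20) × √(effective n / 2) − 1.96].

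- m = 6.5 (one GP): 60 / 1.275 = 47.1; power 95%
- m = 13 (two GPs): 60 / 1.60 = 37.5; power 90%
- m = 19.5 (three GPs): 60 / 1.925 = 31.2; power 84%

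If the cluster size is also reduced by the 30% dropout, the last two become about 93% and 90%. If patients of different GPs in one practice were less correlated than 0.05, the loss would be smaller still. All of these are normal approximations.

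**The case against.** The strongest reply is that the inconsistency may be one of words only. The sample size section treats a practice and a GP as the same thing, and Randomization and blinding has practitioners recruit within their own practices. Both read most naturally as one GP per practice. In that case no practice can be split and every figure stands. This is a fair reading, and it limits the weight of the point. It does not remove it, because the article states no such restriction and sets no criteria for GPs.

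A reader might be tempted to go further in four ways. The documents do not support any of them.

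- **That the clustering level of the analysis is wrong.** Data analysis names no level, so there is none to be wrong. A hierarchical model could use the GP, the practice or both.
- **That standard errors would be too small.** Clustering by GP understates the error when colleagues share an arm. If they are split, a positive practice-level correlation cancels in the treatment contrast, and a GP-level model tends to be conservative. Contamination and understated error therefore do not arise from the same split practice.
- **That type I error is inflated because there are only about 20 clusters.** The article states no normal-theory cut-off, and the choice of reference distribution is commonly left to the analysis plan.
- **That a definite share of the effect would be lost.** The documents give no basis for a contamination rate, do not say that patients see more than one doctor, and send tutorial access only to GPs of the intervention group.

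Nor does the biased coin necessarily split colleagues. It favours whichever arm is behind overall, which may be the arm the last GP joined.

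**Conclusion.** The point holds as an inconsistency in the current text with a missing safeguard. Two sections name different randomisation units, a third moves between them, and no rule covers GPs who share a practice. Contamination of the control arm is possible under the text as written, but the documents do not show that it would occur, and its size cannot be estimated from them.

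The numerical consequence is conditional. With one GP per practice it is nil. With two GPs per practice kept together, power at 60 analysed patients per arm falls from about 95% to about 90% (93% if clusters shrink with dropout), given 6.5 patients per GP and an ICC of 0.05 across the practice. The change is worth making because it is cheap and has to be settled before allocation.

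**What to change.** Use one unit throughout. In Intervention scheme, in Randomization and blinding, and in Power calculation and sample size, state that the practice is randomised. Add either that all participating GPs of a practice are allocated together to one arm, or that only one GP per practice enrols. Express the recruitment target as a number of practices. In Data analysis, name the practice as the cluster level of the hierarchical model.

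If each practice contributes one GP, this costs a few sentences and no number changes. If practices may contribute several GPs, keeping them together gives fewer and larger clusters. The sample size should then be recalculated with the expected number of patients per practice, and either the recruitment target or the stated 95% power revised. Restricting enrolment to one GP per practice avoids that recalculation, but interested colleagues would be turned away.

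### GPs are told their arm before they select and consent their own patients, so the primary comparison is open to recruitment bias of unknown size and direction

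*Protocol article*

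**What the plan says.** The section Randomization and blinding of the protocol article sets out these steps.

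- **Allocation on agreement:** "GPs, who agree to participate, will be sequentially allocated to either the intervention or the control group". Enrolment of patients is not a precondition.
- **Disclosure:** "Participating GPs will be informed about allocation to control or intervention group after randomization completion by postal mail including a sealed envelope". The section also concedes that "it is not possible to blind GPs to their group allocation".
- **Recruitment material:** "They will further be sent recruitment material and consent forms for patients by postal mail".
- **Selection and approach by the GP:** "Practitioners will identify and recruit patients according to the inclusion and exclusion criteria within their practices", followed by "They will inform eligible patients about the study and ask them to participate".

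The section lists several protections. Patients do not know the arm, their information and consent forms are the same in both arms, GPs are not told the primary outcome measures, and the statistician is unaware of allocation. It also says that "GPs will receive an instruction how to recruit patients in a blinded manner", without explaining how.

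Elsewhere, Table 1 makes exclusion depend on an acute illness that would "make study participation impossible according to the GP". The sample size section expects 6–7 patients per practice. The Data analysis section adjusts for the baseline outcome and for confounders, with age, sex and socio-economic background given as examples.

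**The concern.** Randomising practices balances practices. It balances patients only if they are identified before allocation is known, or by someone unaware of it. Here the recruiter knows the arm, has some judgement over exclusion, and follows no stated rule for whom to invite. A GP expecting a weight-counselling tutorial may approach different patients from a GP on a waiting list, for example those more ready to discuss weight.

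The primary outcome is the patient's report of how often that same GP's care over the past six months matched the 5As. A difference in patient mix could therefore appear as a treatment effect or mask one. An intention-to-treat analysis cannot repair this, because the difference arises at entry.

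**Working it through.** **1. Order of events.** The section gives agreement, allocation, letter with envelope, recruitment material, then identification and invitation by the GP. No sentence places patient identification or consent before disclosure, and none gives the task to someone unaware of the arm. No instruction says to leave the envelope unopened until recruitment ends.

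**2. Each safeguard against the mechanism.**

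| Safeguard | Hides the arm from the recruiter? | What it does |
|---|---|---|
| Patients blinded, identical material | No | Limits differential consent and reporting |
| GPs not told the primary outcome | No | Makes it harder to select on that outcome |
| Telephone instruction by an assistant outside enrolment tracking and data collection | No | Separates instruction from tracking |
| Statistician unaware of allocation | No | Protects the analysis |
| Instruction on blinded recruitment | Not as explained | Can mean not revealing the arm to patients |
| Baseline adjustment | No | Removes the part of a difference that the covariates capture |

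**3. The plan's own figure.** With a 15-point difference, SD 20, 95% power and two-sided 5%, n per group = 2 × (1.960 + 1.645)² × (20/15)² = 46.2, so 47. This matches the stated 47, so the SD of 20 and the two-sided 5% level are used below.

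**4. Illustration of sensitivity.** Inputs from the sample size section are 172 patients, 20 GPs, 30% drop-out, ICC 0.05 and SD 20. Assumptions are one GP per practice, equal practices, no true effect, and a residual selection difference b, for which the article gives no value.

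- Completers: 172 × 0.7 = 120.4, which is 60.2 per arm and 120.4/20 = 6.02 per practice.
- Design effect: 1 + (6.02 − 1) × 0.05 = 1.251.
- Effective n per arm: 60.2/1.251 = 48.1.
- Standard error of the arm difference: 20 × √(2/48.1) = 4.08 points.
- Probability of a significant result: Φ(b/4.08 − 1.96) + Φ(−b/4.08 − 1.96).

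| b (points) | Probability of a significant result |
|---|---|
| 0 | 5% |
| 3 | 11.4% |
| 5 | 23.2% |

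With 66 analysed per arm and 6.6 per practice, the design effect is 1 + 5.6 × 0.05 = 1.28. The standard error is 20 × √(2 × 1.28/66) = 3.94, and b = 5 gives 24.6%. The result is not sensitive to that choice.

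The calculation uses the unadjusted SD. Baseline adjustment would shrink b by an unknown amount. It would also shrink the standard error, and a given remaining b would then produce more false positives.

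**The case against.** The strongest reply has four parts.

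**Measured confounders.** The patient questionnaires include readiness to change (Readiness Ruler and stages of change). Under the heading for covariates they also ask about recent GP contacts and whether weight was discussed. These address the likely selection mechanism, and the list of adjustment variables is open. This stands in part: the data exist, but these variables are not named as covariates, and adjustment removes only what is measured.

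**Order not dated.** The sequence is read from prose, and the figure with the intervention scheme is not shown. The word introducing the recruitment material may only mean that it is sent as well. That is fair, but no text supports the opposite order, and the section says outright that GPs cannot be blinded. Tutorial access does wait for a baseline questionnaire, but that delays the training and not the knowledge of the arm.

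**Blinded recruitment.** The phrase may mean only that GPs must not reveal the arm to patients. That reading is reasonable, and the sentence need not be false. It still leaves the recruiter unblinded.

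**Condensed article.** A sampling rule might sit in a fuller protocol. That may be so, and the missing rule alone would be a small matter. The order of disclosure and recruitment, however, is stated in the article itself.

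A reader might go further and infer that GPs will hand-pick favourable patients from a large pool and that the bias will favour the tutorial. The article does not support this. It gives no pool size, and GPs must apply the stated criteria. The score reports how often elements of care occurred and does not rate the relationship. Patients with whom weight is already discussed might start higher and have less room to improve, so the direction is open.

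**Conclusion.** The point holds as a weakness of design: followed as written, the plan lets an unblinded GP recruit after allocation, so the primary comparison is open to recruitment bias. Neither its size nor its direction can be established from the article, and the text does not show that bias will occur. The 11% and 23% figures rest on assumed differences of 3 and 5 points remaining after adjustment. They show how sensitive a trial of this size is and are not a forecast. The stated safeguards reduce the risk without removing its source. This should be fixed, ideally before recruitment, because selection at entry cannot be undone later. It does not by itself invalidate the trial.

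**What to change.** Keep the sequential biased-coin allocation by staff outside the project and change when it takes effect. Do not allocate a practice, or at least do not send it the allocation letter, until it has:

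1. listed its eligible patients;
2. invited them consecutively, or in random order from the list;
3. obtained consent, preferably with the patient baseline questionnaires returned.

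State that this is what blinded recruitment means. Name baseline readiness to change and prior weight discussion with the GP as adjustment covariates, alongside the baseline 5A PACIC score and the demographic factors. Both are already collected.

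**Cost.** No extra patients or study staff are needed, but practices must draw up a list and GPs learn their arm some weeks later. Some may withdraw, which matters with about 20 GPs. The Strengths section gives quick recruitment and avoiding GP withdrawal as reasons for the randomization method. Delaying only the disclosure largely respects this, since the sequential method is unchanged and tutorial access already waits for a baseline questionnaire.
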